## Methods

This protocol adheres to the reporting recommendations relevant specifically to an observational retrospective cohort study of the Guidelines for Reporting Outcomes in Trial Protocols: The SPIRIT-Outcomes (2022), obtained via the Equator Guidelines [12]. Consultation with doctors in the field of general surgery and rural health experts from WACHS was performed in the development of this protocol to ensure that the needs of rural populations are not misrepresented.

The study design was chosen to be retrospective due to the difficulties of prospective recruitment by medical student data collectors for whom it is unrealistic to conduct a prospective study to recruit appendicitis patients due to the transient nature of placements, especially in large metro hospitals, which would likely lead to selection bias (for more details, see “Collaborative teams”). Four separate 2-week data collection periods were preferred over one asynchronous period of data collection to provide structure for the data collection into four 6-month retrospective review periods which would allow more medical students to participate in data collection in the project overall if each student is allocated one data collection period and to divide the amount of retrospective data to be reviewed into a manageable amount for each mini-team (for more details see “Collaborative teams”).

The retrospective time period which will be examined for eligible patients and from which data is collected will be over a 2-year period from January 2022 to November 2023. Appendicectomy patients will be identified from the operating room register by members of the mini-teams discussed in the “Methods” section, expected to be mainly medical student data collectors currently on placement at the relevant hospital, and then, each respective hospital’s emergency room data collection subsequently will be accessed to fill out the case report forms. The data will be collated via case report forms based on demographics and clinical findings, pre-operative investigations, and management and follow-up. Case report forms with > 95% completeness will be accepted for pooled analysis. The expected duration of retrospective data collection will be 8 months. This includes the four 2-week data collection periods.

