The planned first data collection period will only record information for eligible patients receiving appendicectomy at the relevant center between January and June 2022 retrospectively to their surgeries being performed, and then, a check of the patient’s record until the 30-day postoperative interval on the same data collection source will be conducted to record any readmissions or complications.

The planned second data collection period will only record information for eligible patients receiving appendicectomy at the relevant center between June 2022 and December 2022 retrospectively to their surgeries being performed, and then, a check of the patient’s record until the 30-day postoperative interval on the same data collection source will be conducted to record any readmissions or complications.

The planned third data collection period will only record information for eligible patients receiving appendicectomy at the relevant center between January 2023 and June 2023 retrospectively to their surgeries being performed, and then, a check of the patient’s record until the 30-day postoperative interval on the same data collection source will be conducted to record any readmissions or complications.

The planned fourth data collection period will only record information for eligible patients receiving appendicectomy at the relevant center between June 2023 and November 2023 retrospectively to their surgeries being performed, and then, a check of the patient’s record until the 30-day postoperative interval on the same data collection source will be conducted to record any readmissions or complications.

For the purpose of this project, sites under WA Country Health Service (WACHS) jurisdiction will be considered rural, that is, Albany Hospital, Bunbury Hospital, Broome Health Campus, Geraldton Hospital, and Hedland Health Campus. The other sites (Royal Perth Hospital, Sir Charles Gairdner Hospital, Fiona Stanley Hospital, Armadale Health Service) will be considered urban.

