### Data collection and storage

Data will be collected and stored online through a secure server running the Research Electronic Data Capture (REDCap) web application. REDCap allows collaborators to enter and store data in a secure system. Collaborators will be given individual REDCap login details, allowing secure data storage on the REDCap system. No identifiable patient information will be collected. Collaborators may wish to first record data on a paper version of the data collection pro-forma. Paper copies of any data should be destroyed as confidential waste within the center once uploaded to REDCap.

Identifiable patient information will not be entered into REDCap since only the case report forms will be completed for every eligible instance of appendicectomy surgery.

Essentially, this study involves nothing from the participants themselves at all, only a retrospective review of their surgery admission. A report of the study will be sent to a medical journal approximately 4 months following completion of data analysis, and due to patient anonymity, they will not be informed of the outcomes of the project.

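### As written, June 2022 and June 2023 each fall in two collection periods, so the same operation can be entered twice in a database without patient identifiers

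*Protocol article*

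**What the plan says.** All references are to the protocol article.

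The Methods section defines four collection periods by month of surgery, without days:

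- Period 1: "eligible patients receiving appendicectomy at the relevant center between January and June 2022"
- Period 2: "eligible patients receiving appendicectomy at the relevant center between June 2022 and December 2022"
- Period 3: "eligible patients receiving appendicectomy at the relevant center between January 2023 and June 2023"
- Period 4: "eligible patients receiving appendicectomy at the relevant center between June 2023 and November 2023"

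The same section calls these "four 6-month retrospective review periods" and gives the overall window as January 2022 to November 2023, described as two years. It explains that separate periods let more students take part if each is given a single period. Cases are found from each hospital's operating room register.

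Under Data collection and storage the article says: "No identifiable patient information will be collected". One case report form is to be completed for each eligible operation. Paper forms are optional and are destroyed after upload.

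The primary outcome section says that presentation, diagnosis and surgery are recorded as date and time. The case report forms also hold demographics.

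**The concern.** June 2022 closes period 1 and opens period 2; June 2023 closes period 3 and opens period 4. Collectors who follow the wording literally in successive periods would both take June operations from the same register. With no patient identifier in the database, a repeat cannot be matched on identity when the data are pooled, and the article describes no check for a case already entered.

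Undetected repeats would give June patients double weight in every rate, mean and median, and would inflate the reported sample size. The planned t-tests, Mann–Whitney tests and chi-squared tests treat each row as an independent patient, so their standard errors would be too small.

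**Working it through.** **1. The plan's own sample size.** The Sample size section gives 818 claims in a year, doubled for two years: 2 × 818 = 1,636. The site allocations give 4 × 350 + 5 × 50 = 1,650. Both agree with the stated figure of over 1,600.

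**2. Calendar count, named months included.**

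| Period | Months named | Count |
|---|---|---|
| 1 | Jan–Jun 2022 | 6 |
| 2 | Jun–Dec 2022 | 7 |
| 3 | Jan–Jun 2023 | 6 |
| 4 | Jun–Nov 2023 | 6 |
| Total | | 25 |

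January 2022 to November 2023 is 12 + 11 = 23 months. The excess is 25 − 23 = 2 months, namely the two Junes.

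**3. Whether another reading removes the overlap.** Periods 2 and 3 meet cleanly at December 2022 and January 2023, which supports reading the named months as included. Excluding every closing month would lose December 2022 and November 2023. Excluding every opening month would lose January 2022 and January 2023. So each uniform whole-month rule either covers two months twice or omits two. A boundary inside or at the end of June would remove the overlap, but the text states none. Four six-month periods need 24 months and the window has 23, so that description cannot hold exactly on any non-overlapping split.

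**4. Largest number of extra rows.** Assume even monthly volume, every June case entered twice and none removed.

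- Site total: 1,650 × 2/23 = 143.5, about 143 extra rows. Urban: 1,400 × 2/23 = 121.7; rural: 250 × 2/23 = 21.7.
- Claims rate: 818/12 = 68.2 per month, and 2 × 68.2 = 136 extra rows.
- Share of all rows: (2/23)/(1 + 2/23) = 2/25 = 8.0%.

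**5. Effect on standard errors and tests.** Let a fraction f of n unique patients appear twice, so that there are n(1 + f) rows. The true variance of the mean is σ²[(1 − f) + 4f]/[n(1 + f)²] = σ²(1 + 3f)/[n(1 + f)²]. The variance computed under independence is σ²/[n(1 + f)]. Their ratio is R = (1 + 3f)/(1 + f). If f is the same in both groups, R also applies to the rural–urban difference. The actual size of a nominal two-sided 5% test is 2[1 − Φ(1.96/√R)]. The article gives 0.05 without sidedness; two-sided is assumed.

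| June cases duplicated | f | Extra rows (of 1,650) | R | √R | Actual size |
|---|---|---|---|---|---|
| All | 2/23 | 143 | 1.160 | 1.077 | 0.069 |
| Half | 1/23 | 72 | 1.083 | 1.041 | 0.060 |
| A tenth | 0.2/23 | 14 | 1.017 | 1.009 | 0.052 |
| None, or all removed | 0 | 0 | 1.000 | 1.000 | 0.050 |

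In the first row, 1/1.077 = 0.928, so the computed standard error is about 7% too small.

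**The case against.** A reader might infer that June patients will be entered twice and analysed as different people, and that this could not be undone after pooling. The documents do not support that.

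- Without days, the wording could mean a boundary within or at the end of June. The stated purpose of the periods is to divide the work, and one form is called for per operation.
- The allocation of one period to each student is conditional. The mini-teams belong to a site, and a consultant local lead coordinates each centre, so someone may notice that June has been done.
- Excluding identifiable information does not exclude a non-identifying study number. Dates and times of presentation and surgery, with demographics, should expose most repeats within a hospital, and the register remains available for checking. A repeat that one query can find is not hard to reverse.
- A duplicate check may be in the full protocol or a data-management plan, neither of which is shown. Its absence from an article is not a fault.
- If rural and urban sites duplicate to a similar degree, the comparison is not biased, and nothing in the article suggests that they would differ.

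These points stand. They limit the finding to a risk and make the figures above an upper limit. They do not remove the stated overlap or its conflict with four six-month periods, and two sites could resolve the ambiguity differently.

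**Conclusion.** The concern holds as an error in the stated dates that creates a risk of double entry. Its size ranges from zero to about 143 extra rows, or about 8% of the pooled data. The upper limit rests on even monthly volume, the planned 1,650 patients over 23 months, complete duplication of both Junes and no removal; on the claims rate it is about 136 rows. That rate is a statewide figure, not a count from the nine sites. The test sizes further assume equal duplication in both groups and take no account of clustering by hospital. The consequence is mainly false precision and an inflated sample size, not a biased rural–urban comparison.

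**What to change.** Define the periods by exact date of surgery, without overlap:

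1. 1 January to 30 June 2022
2. 1 July to 31 December 2022
3. 1 January to 30 June 2023
4. 1 July to 30 November 2023 (taking the stated November end as the last day of the month)

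Describe the window as 23 months, with periods of 6, 6, 6 and 5 months. Align the Sample size section, which takes the window to the end of 2023.

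Before pooling, run one duplicate check within each site on date and time of surgery and of presentation plus demographics (age and sex are assumed to be among them). Confirm matches against the site's register and keep one record per operation.

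The cost is a few edited dates and one data-cleaning query. The design and the data to be collected do not change.

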It is hypothesized that there will be a higher rate of negative appendicectomies in rural hospitals as opposed to metropolitan hospitals, rooting from various potential factors. According to an audit examining the rural–urban differences in surgical interventions in the United States (US), there were higher rates of an array of surgeries including appendicectomies in areas classified rural according to US standards. This was contrary to the authors’ hypothesis that rurally located patients would have lower surgical rates. The authors proposed this could be explained by rural patients experiencing overall poorer health, increasing the indications for many surgeries to be undertaken [8]. This can be extrapolated to the Australian setting, where, according to the Australian Institute of Health and Welfare (AIHW), risk factors such as smoking, obesity, and hypertension amongst many others all increased with rurality, as well as chronic health conditions and burden of disease [9]. Another factor which may contribute to potential higher negative appendicectomies is that doctors may have a lower threshold to perform the surgery in order to avoid potential severe complications, such as perforation in a setting where there is reduced healthcare access. This may in turn lead to reduced surgical wait times in rural settings, addressing both our primary and secondary outcomes. Another US study on pediatric patients revealed that rural hospitals were 50% more likely to perform negative appendicectomies. The authors explained this is due to negative appendicectomies being justified in order to “decrease delay in diagnosis and subsequently lower the risk of appendiceal perforation” [10]. The authors noted that this disparity may also be in part due to reduced access to pre-operative imaging such as computed tomography to make the diagnosis. It is suspected a combination of all stated factors may play a role in reduced surgical wait times and negative appendicectomies in rural compared to metropolitan hospitals in Western Australia.

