### Primary outcome measure

Wait time from presentation (hours) to diagnosis and then surgery. This is the number of hours from initial presentation at an emergency department until review by the surgical team, diagnosis, and then surgery. These parameters will be recorded on the case report forms as date and time and will be used to compare such wait times between rural and metropolitan hospitals.

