Following data collection, only case report forms with > 95% data completeness will be accepted for pooled analysis. Centers with > 5% missing data points will be excluded and collaborators from those centers withdrawn from the published list of citable collaborators. This is in order to provide some leeway for potential missing data, while also acknowledging that case report forms with ≥ 5% missing data may not be useful for our purposes. As the data originates from emergency department records, there is no perceived risk of including false or unused data. This study RGS6483 has received HREC approval by the Royal Perth Hospital HREC Ethics Committee, with a waiver of consent obtained and the HREC was notified of amendments to the protocol made on April 21, 2024.

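### The 95% form rule and 5% centre rule discard patients whose outcomes are recorded, select by documentation quality, and so put the rural-urban comparison at risk of bias

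*Protocol article*

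**What the plan says.** The Methods section sets two filters.

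- **Form rule.** Only forms with more than 95% "data completeness will be accepted for pooled analysis". The Abstract repeats this. The form covers "demographics and clinical findings, pre-operative investigations, and management and follow-up", so completeness is judged over all of that content.
- **Centre rule.** Centres with more than 5% "missing data points will be excluded and collaborators from those centers withdrawn" from the list of citable collaborators.

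The reason given is that forms with 5% or more "missing data may not be useful for our purposes". The article adds that, because the data come from emergency department records, "there is no perceived risk of including false or unused data".

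The primary outcome needs far less than the whole form. Under Primary outcome measure, the times of presentation, surgical review, diagnosis and surgery are the inputs: "These parameters will be recorded on the case report forms as date and time", and they "will be used to compare such wait times between rural and metropolitan hospitals". The Criteria section admits all patients aged 16 or older who have an appendicectomy in the study period, apart from two exclusions (prior appendix or colon resection, and pregnancy).

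**The concern.** A patient with every timestamp and a histology result is dropped from every analysis if enough unrelated items are blank. For that patient, the stated reason that the form may not be useful is wrong as regards wait time and negative appendicectomy. The centre rule goes further, because a hospital that fails on average loses its complete forms as well.

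The analysed group is then no longer the eligible cohort but the well-documented part of it. The data are routine records, abstracted by a different team at each hospital, and the study compares hospitals. Completeness could therefore plausibly differ between the groups being compared. The Methods section defends the retrospective design partly because prospective recruitment would invite selection bias, yet these filters bring in a selection step of their own. The statement about false or unused data concerns what is let in, not what is left out.

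At stake are the primary wait-time contrast, the negative appendicectomy rates, and the small set of rural hospitals on which both depend.

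**Working it through.** **1. The plan's own figure.** Sample size section: 818 claims × 2 years = 1,636. By centre: 4 × 350 + 5 × 50 = 1,400 + 250 = 1,650. Both agree with the stated total of over 1,600.

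**2. Loss of a centre.**
- One rural centre: 50/250 = 20% of rural patients, and one of five rural sites.
- One urban centre: 350/1,400 = 25% of urban patients, and one of four urban sites (350/1,650 = 21% of all patients).

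**3. What that does to precision.** The article gives no effect size or power. Assume a two-sided 5% level, 80% power, a true difference of 0.20 SD, and no clustering by hospital.

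Detectable difference in SD units = (1.960 + 0.842) × √(1/n_rural + 1/n_urban). Power at 0.20 SD = Φ(0.20/√(1/n_rural + 1/n_urban) − 1.960).

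| Centres lost | Rural | Urban | Detectable (SD) | Power at 0.20 SD |
|---|---|---|---|---|
| None | 250 | 1,400 | 0.192 | 83% |
| One rural | 200 | 1,400 | 0.212 | 75% |
| Two rural | 150 | 1,400 | 0.241 | 64% |
| Three rural | 100 | 1,400 | 0.290 | 49% |
| One urban | 250 | 1,050 | 0.197 | 81% |

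**4. Loss of forms.** The number of fields m and the missing rate q per field are not given. Assume m = 30 to 60 and q = 2% to 4%, with fields missing independently. A form fails when missing fields/m ≥ 5%, that is at 2 or more of 30, 2 or more of 40, or 3 or more of 60. P(fail) = 1 − Σ C(m,x) q^x (1−q)^(m−x), summed over the permitted x.

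| Fields | q = 2% | q = 4% |
|---|---|---|
| 30 | 12% | 34% |
| 40 | 19% | 48% |
| 60 | 12% | 43% |

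A hospital averaging 4% missing passes the centre rule and still loses 34-48% of its forms. The result depends on the field count: with 20 fields a single blank fails the form (33% and 56% lost), while with 80 fields the losses are 8% and 40%.

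**5. How the two rules fit together.** After the form rule, every kept form has less than 5% missing, so no centre's average can exceed 5%. The centre rule can therefore act only on unfiltered data, where it removes forms that had passed.

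**6. When bias arises.** Illustration only: identical log-normal waits in both groups (median 18 h, SD 0.6 on the log scale). The chance of exclusion at the median wait is 10% in one group and 30% in the other, and its log-odds change with each SD of log wait.

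| Change in log-odds per SD | Excluded | Median wait kept | Spurious difference |
|---|---|---|---|
| 0 | 10% v 30% | 18.0 v 18.0 h | none |
| +0.5 | 11% v 31% | 17.45 v 16.51 h | 0.9 h |
| +1.0 | 13% v 33% | 16.86 v 15.34 h | 1.5 h |
| −0.5 | 11% v 31% | 18.58 v 19.65 h | 1.1 h, opposite sign |

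Unequal exclusion alone does not shift the medians. A shift needs exclusion to be related to the wait itself, and to a different extent by group.

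**The case against.** The strongest reply is that a completeness threshold is a reasonable data-quality safeguard for student-collected records, and that nothing in the article shows it does harm. No missingness figures are given. The form-loss calculation assumes independent, random blanks. Under that assumption the rule costs precision but causes no bias, and if blanks cluster in a few forms fewer forms fail at the same average. Losing an urban centre barely moves the power. All of this stands, and it limits the point to certain data loss for any form or centre affected, plus a risk of bias.

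Three stronger readings are tempting and are not supported:

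- **That the comparison is biased.** The illustration gives no bias, or bias in either direction, depending on a relation that the article does not describe.
- **That less rural imaging will leave more blanks at rural sites and in negative cases.** The Introduction mentions "reduced access to pre-operative imaging such as computed tomography to make the diagnosis", but as a remark by the authors of a US paediatric study, which the plan takes up only tentatively. It says nothing about missing records, and this study enrols from age 16. The route also needs undone tests to be left blank, and the form is not shown. One can construct an example: a true negative rate of 30%, with form failure in 40% of negative and 20% of other cases, gives 0.18/(0.18 + 0.56) = 24.3%. Nothing in the document supports those failure rates.
- **That linking authorship to accepted data will lead collectors to fill blanks.** The link is there, but nothing suggests that entries would be invented, and each centre has a supervising surgical consultant. This is a governance question, separate from the estimate.

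The reply that a separate analysis plan may deal with missing data does not remove the point. The exclusion is fixed in the protocol text, and the Data analysis section says there are no plans to deviate from the statistical plan.

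**Conclusion.** The point holds as a badly fixed analysis rule. Discarding recorded outcomes follows directly from the wording and rests on no assumption. The centre losses (20% of rural or 25% of urban patients per centre) use the plan's own numbers. The precision cost falls mainly on the rural side: at an assumed 0.20 SD, power drops from 83% to 75% with one rural centre lost, against 81% with one urban centre lost. The 12-48% form loss depends on the assumed field count, missing rate and independence, and should be read as a range of what could happen.

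Bias in the rural-urban contrast is a plausible risk of unknown size and direction. It requires completeness to be related to wait time or case type differently by region, or an excluded centre to differ from the others in its group. If neither is so, the rules only waste information.

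**What to change.** Change the protocol wording before any forms are filtered:

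- For the primary outcome, analyse every eligible patient who has the timestamps needed. For each secondary outcome, analyse every patient with that outcome recorded.
- Report completeness by hospital and region, and compare the patients whom the present rules would exclude with those whom they would keep.
- Keep the 95% form rule and the 5% centre rule only as a trigger for data queries and as a sensitivity analysis.
- Confirm that a test recorded as not done counts as a completed answer. The form may already do this.

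Imputation is not needed for the unadjusted tests now planned. It becomes relevant only if a covariate-adjusted analysis is added.

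The cost is a change of wording and slightly more analysis work, with no extra data collection. The downside is that some less complete records enter the main analysis.

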#### Mini-teams

Mini-teams consist of five collaborators at each site whose role is to identify eligible patients receiving appendicectomies during the study periods and collect data. The mini-teams are planned to consist mainly of student data collectors who are currently on placement at the relevant hospital, recruited through the student research network STRIVE WA. One collaborator is to be selected as the local lead. For every center, there is to be a local lead in the form of a surgical consultant, who coordinates and supervises the actions of that center. All collaborators part of a mini-team whose data is accepted for the final pooled analysis will be listed as co-authors on the final manuscript.

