### Criteria

Inclusion criteria:(i)All patients who undergo an appendicectomy during the study period.(ii)Age 16 years or older at time of presentation

Exclusion criteria:(i)Previous appendicectomy or right hemi-colectomy or total colectomy.(ii)Current pregnancy at time of presentation

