### Data analysis

Normally distributed data will be reported as mean (standard deviation (SD)), and non-normally distributed data will be reported as median (interquartile range (IQR)). Independent *t*-tests or ANOVAs will be used for normally distributed variables, Mann–Whitney *U* and Kruskal–Wallis tests will be used for non-normally distributed continuous or ordinal variables, and chi-squared tests will be used for categorical variable comparisons. When comparing appendicectomy wait times with complication incidence during the data analysis phase, a *P* value of 0.05 will be used to determine statistical significance. There will be no interim analysis or audit planned due to the grouping of data sets over four data collection periods. As this is a retrospective observational cohort study, there are no plans to deviate from the original protocol statistical plan or study design.

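### Centre acceptance and authorship depend only on missing items in submitted forms, never on register coverage, so the all-patients cohort can become a selected one with uncounted losses

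*Protocol article*

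**What the plan says.** The target cohort is a census. The first inclusion criterion (Criteria) is "All patients who undergo an appendicectomy during the study period", limited to those aged 16 or older and subject to two exclusions.

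Methods sets two completeness rules:
- **Form level:** "only case report forms with > 95% data completeness will be accepted for pooled analysis".
- **Centre level:** "Centers with > 5% missing data points will be excluded", with "collaborators from those centers withdrawn from the published list of citable collaborators".

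The matching reward is under Mini-teams: "All collaborators part of a mini-team whose data is accepted for the final pooled analysis will be listed as co-authors".

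Case finding and data entry are in the same hands. Methods states that "Appendicectomy patients will be identified from the operating room register by members of the mini-teams", and Mini-teams describes a group "whose role is to identify eligible patients receiving appendicectomies during the study periods and collect data". A surgical consultant leads and supervises at each centre. No count of register cases against forms is described. Data analysis adds that "There will be no interim analysis or audit planned", giving as the reason that the data are grouped over four collection periods.

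**The concern.** Both rules score the forms that a team chose to submit. A patient who was never entered adds no missing items, so poor case ascertainment cannot lower either score, while honest entry of a poorly documented patient can. The team that decides whom to enter is the team whose authorship depends on the result.

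The comparisons of wait times and of negative appendicectomy rates between rural and urban hospitals are meant to rest on all eligible operations. If poorly documented patients are left out, or their blanks are filled with guesses, the analysed set is no longer that cohort, and a reader cannot see how many are missing or from which sites. If a team does enter them, the study may lose the whole centre. Methods justifies the retrospective design partly by the selection bias expected from prospective recruitment by students, so it matters that the acceptance rule does not open another route to selection.

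**Working it through.** **1. The plan's own figures.** Sample size gives over 1600 participants. Doubling the annual claims gives 818 × 2 = 1636. Summing the sites gives 4 × 350 + 5 × 50 = 1400 + 250 = 1650. Both agree with the stated total, which is not in dispute. The site figures of 350 and 50 are used below.

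**2. Over which forms is centre missingness counted?** Methods does not say. Suppose it is counted only over accepted forms. Each of those is more than 95% complete, so each has less than 5% missing, and so does any average of them. No centre could then exceed 5%, and the centre rule would have no effect. The rule can act only if it is counted over all submitted forms, before the form filter. That is the reading used here.

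**3. What a team faces with a thin record** (a form that cannot honestly pass 95%):

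| Team's action | Patient analysed? | Effect on centre missingness |
|---|---|---|
| Enters it as found | No, the form filter drops it | Rises, towards exclusion |
| Does not enter it | No | None |
| Fills the blanks | Yes, with values not in the record | No missing items added |

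Only the first action can cost the team its centre and its authorship, and it gains the team nothing.

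**4. Illustration.** The document gives no missingness rates. Assume ordinary forms are 2% missing and thin forms 30% to 50% missing. With n eligible patients, of whom k have thin records, centre missingness with everyone entered is [(n − k) × m0 + k × m1] / n. With the thin records left out it is m0.

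- Rural site, n = 50, k = 5, m1 = 40%: (45 × 2% + 5 × 40%) / 50 = 5.8%, excluded. Left out: 2.0%, kept, with coverage 45/50 = 90%.
- Rural site, k = 4: (46 × 2% + 4 × 40%) / 50 = 5.04%, already over the limit.
- Metropolitan site, n = 350, k = 35: (315 × 2% + 35 × 40%) / 350 = 5.8%, against 2.0% when left out.
- Share of thin records at which a centre reaches 5%, from (5% − 2%) / (m1 − 2%): 10.7% at m1 = 30%, 7.9% at 40%, and 6.3% at 50%.

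**5. What the omission changes.** In the metropolitan example the form filter drops the 35 thin forms if they are entered, and they are absent if they are not. As long as the centre stays in, the same 315 patients are analysed. The rule's own added effects are therefore:
- the 35 are no longer counted as lost;
- guessed values may enter where blanks were filled;
- if the 35 are entered, all 350 patients go with the centre.

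Losing one rural site removes 50/250 = 20% of the planned rural patients. Losing one metropolitan site removes 350/1400 = 25% of the planned urban patients.

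**The case against.** Several points on the other side have force.

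- **The form filter does the selecting.** A reader might infer that the authorship rule itself biases the negative appendicectomy rate by, say, 10% omitted × a 10-point difference = 1 point, up to 20% × 15 points = 3 points. The documents do not support that. The inputs are assumptions, and the openly stated form filter removes the same thin records whether or not they are entered. If the omitted patients resemble the rest, there is no bias. This objection stands.
- **The order of the two rules is not stated.** If the centre rule is applied after the form filter, the authorship threat vanishes. That is so, but the centre rule then does nothing, which is unlikely to be intended.
- **Omission would leave a trace.** A reader might infer that it could never be detected, from the destruction of paper copies and the absence of identifiers in REDCap (Data collection and storage). That goes too far. The register and hospital records remain, a large shortfall from 350 or 50 might be noticed, and a consultant supervises each centre. What stands is narrower: none of these is specified as a check, and the site figures are round planning estimates.
- **The audit sentence is weak evidence.** The word interim may govern both nouns, and the reason given concerns the collection periods. It should not be read as ruling out checks of the final data.
- **The article is condensed.** A screening log or a not-documented response option may exist in the full protocol or on the form. The point therefore rests on the acceptance and authorship rules that the article itself fixes.
- **Nothing shows that teams will omit or guess.** This is correct. It is an inference from the incentive, so the cohort can become selected; the text does not show that it will.

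**Conclusion.** The concern holds as a badly set acceptance and authorship rule. Centre inclusion and authorship depend only on item missingness in submitted forms, so a thin record cannot help a team and can cost it the centre. This works against the all-patients cohort, and no comparison with the register is described that would show the loss. Because the form filter already removes such records, the added harm is mainly hidden non-ascertainment, guessed values or loss of a whole centre.

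In the illustration, omitting 10% of patients moves a centre from 5.8% missing (excluded) to 2.0% (accepted), with the missing tenth invisible to either score. This assumes the stated missingness rates and that centre missingness is counted over all submitted forms. The size and direction of any bias in wait times or negative appendicectomy rates cannot be derived from the document. The rule should be changed before forms are accepted for pooled analysis.

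**What to change.** In Methods and Mini-teams:

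1. For each site and collection period, record and publish three counts: eligible cases on the operating room register, forms entered and forms analysed.
2. Make acceptance and authorship depend on case ascertainment (forms entered divided by eligible register cases), and not on item missingness alone.
3. Count an explicit entry of 'not documented in record' as a completed answer when scoring completeness, and treat such items as missing in the analysis. Honest entry of a thin record then excludes neither the patient nor the centre.
4. State over which forms centre missingness is counted.

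The cost is one extra count per site and period from a register that is already being read, one response option if the form lacks it, and reworded acceptance and authorship rules. The downside is a weaker push to search for missing items.
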